# ReNaApp: increasing the long-term effects of oncological rehabilitation through an application after medical rehabilitation (ReNaApp): a quasi-randomized longitudinal study of prospective design

**DOI:** 10.1186/s12913-020-05248-9

**Published:** 2020-05-06

**Keywords:** Breast cancer, Rehabilitation, Oncological rehab, Quality of life, Participation, Physical activity, Mobile application

## Abstract

**Background:**

Breast cancer is the most common malignant disease in women. Compared with other cancer types, breast cancer has a higher survival rate. The majority of breast cancer patients are overstrained to implement cancer-specific recommendations relating to changes in health behaviour. Numerous epidemiological studies have shown a positive correlation between physical activity and quality of life as well as the course of disease during and after breast cancer treatment. However, many patients have difficulties integrating physical activity into their everyday lives due to cancer symptoms. To develop physical activity into a daily routine, an aftercare programme for breast cancer patients will be developed. In particular, the programme is structured in terms of the validated concept “Neues Credo”. The basic concept is converted into a mobile application.

**Methods:**

The study sample includes *n* = 740 rehabilitants (370 for the intervention group and for the control group) from five different rehab clinics in Northern Germany. The evaluation is as follows: a) Quasi-randomized, prospective longitudinal study (sequential study design). The intervention group receives a mobile application after rehabilitation, and the control group receives treatment as usual. The study evaluation is carried out through a questionnaire at three stages (at the beginning of the rehabilitation, at the end of the rehabilitation, and after 12 months). b) Qualitative analysis of interviews and focus groups in terms of feasibility and acceptance. c) Formative evaluation of the app.

**Discussion:**

Above all, the aftercare programme ReNaApp increases the long-term effects of oncological rehabilitation. By documenting physical activity in ReNaApp, rehabilitants become more motivated to engage in physical activity in their everyday lives. Currently, there is no scientifically evaluated app for breast cancer patients in the German language. Thus, ReNaApp ensures an aftercare treatment for breast cancer patients with high-quality performance regardless of their place of residence. By adopting a participatory approach and a user-centred design, ReNaApp corresponds to the demands of the rehabilitants.

**Trial registration:**

German Register of Clinical Trials, www.drks.de.

Identifier: DRKS00019017; Registered: November 7th, 2019.

Date and version identifier: April 17th 2020; vesion 2.

## Background

With an incidence of 69,000 per year, breast cancer is one of the most common cancers that affect women in Germany [1]. In particular, breast cancer affects one in eight women, and three out of 10 are younger than 55 years old at the time of diagnosis [2]. During recovery, women are faced with symptoms and side effects, including fatigue, weight increase, decrease in muscle strength and bone density, pain, fear and depression, reduction of social and work-related participation and reduction of quality of life [3].

A number of authors have shown that physical activity is one of the most successful strategies in the course of an oncological disease. Physical activities increase the sense of well-being, quality of life and survival rate after cancer [3–6]. Moreover, the ability to work develops with physical activity [7]. Above all, the ability to work plays a crucial role for patients because it is connected with the return to normality. As a result, self-confidence, mental health and quality of life increase steadily [8, 9]. Nevertheless, given the symptoms, e.g., fatigue, weight gain or depression, it is difficult to implement physical activity in everyday life [10].

Medical rehabilitation is one opportunity to initiate an active lifestyle after breast cancer [11, 12]. To transfer the already-gained physical activity from rehab into the domestic environment, rehabilitants need an adequate aftercare programme [11, 12]. Regarding the current legal situation, an aftercare programme for breast cancer patients cannot be offered in Germany. There is, indeed, the chance of rehabilitation sports or functional training, but these often fail due to structural and local conditions.

Although there is no aftercare programme for breast cancer patients, an effective approach for other diseases has been developed. Further studies validated the aftercare concept called “Neues Credo”, which introduces and maintains physical activity. The aim of “Neues Credo” is to increase the physical activity of rehabilitants and help them maintain this increased engagement for long periods [13]. For instance, the concept has been evaluated in clinical trials with orthopaedic and psychosomatic patients and demonstrated long-term effects for rehabilitants [14, 15]. An analysis of a current study with cardiology rehabilitants supposes further success.

The aftercare programme “Neues Credo” contains a complex intervention. First, the rehabilitants obtain coping skills together with other patients during rehabilitation. Simultaneously, the rehab clinics provide an educated aftercare agent whose task is to motivate the patients during and after rehab. In this context, the agents support rehabilitants in achieving their individual goals and maintaining physical activity in everyday life.

While the concept “Neues Credo” only consists of a paper version, mobile applications for healthcare have been increasingly established in recent years. A reason for that is the rising importance of smartphones in the current society. For example, in January 2017, more than 54 million people over the age of 14 owned a smartphone in Germany. In other words, 62% of Germans use a smartphone [16]. In addition to the increase in smartphone users, the use of mobile applications increased up to 52% among individuals in the age range of 40–49 years and 34% among individuals in the age range of 50–59 years, tending upwards [17]. In the present study, “Neues Credo” can for the first time be implemented as a smartphone app, called ReNaApp. This app considers the needs of women with breast cancer.

Recently, there has been a growing interest in mobile health (mhealth) applications that support healthcare services through smartphone/mobile terminals [18]. Actually, the most common play stores have a selection of over 100,000 health apps [19, 20]. Approximately 29% of Germans have installed healthcare apps on their smartphone [19, 20]. However, most freely available apps have a lower quality than apps requiring payment [18, 21]. Many applications are developed outside of the primary health care sector [19, 20] and, unfortunately, lack a theoretical basis. Moreover, there are usually no proof-of-concepts on the efficiency of those tools [18–21].

Due to the great potential of mobile applications in healthcare, a need for evidence-based and high-quality applications arises [18, 21]. Previous reviews emphasized the efficiency of such applications [22–25]. Additionally, randomized clinical trials (RCTs) detected positive effects for patients with different medical indications [26]. Finally, one study observed successful results of a mobile application for breast cancer patients [27]. In conclusion, there is a lack of evidence of high-quality RCTs in this field of research [22–25].

The aftercare programme “Neues Credo” complies with the needed theoretical foundation [28] and has shown significant efficiency in different indications [14, 15]. The present study will modify the concept from paper-based materials into a mobile application and adapt it to the needs of women with breast cancer.

### Aims

This study aimed to integrate more physical activity into the life of breast cancer patients after rehab. (1) During rehabilitation, breast cancer patients are introduced to physical activities, define goals for the time after rehab and finally develop a plan for their implementation. (2) After rehabilitation, the patients install the ReNaApp, which includes an exercise diary, to reach their individual goals. In addition to the diary, the app encompasses tools for individual feedback, motivating functions and a comprehensive information area. (3) Consequently, the aftercare programme ReNaApp increases the physical activity of rehabilitants because of their greater motivation to permanently maintain the achievements of rehabilitation. More specifically, expectations in terms of improved social and professional participation, quality of life, return to work and general health are forecast over a period of 12 months.

### Intervention

Initially, each of the participating clinics chooses one aftercare agent for the whole duration of the project. The agents will be trained concerning the recruiting strategy, the philosophy of the aftercare programme, and the handling of the ReNaApp. During rehabilitation, the intervention group (IG) will be supported by them.

During rehabilitation, the participants of the study will receive a paper-based observation book. The observation book targets good preparation for the time after rehabilitation by the following three tasks: 1) self-monitoring: Which types of physical activity do I enjoy, and which physical activities make me feel good? 2) Which suitable physical activities exist, and which would I like to try? 3) What kind of physical activities are near my home?

At the end of rehab, the patients will be invited to individually plan their physical activity according to their observation books: Which type of physical activities will I integrate and when? Therefore, the rehabilitants join a group for an hour to discuss the observation book with other rehabilitants and therapists. The therapists especially advise the preparation of personal plans for implementation and compliance. Within the group hour, all patients write a letter to themselves, which is sent by the aftercare agents to every patient 3 months post-rehab.

As already mentioned, the aftercare programme encompasses a mobile application. ReNaApp is available on the web page of the involved clinics. During the class hour, the aftercare agents introduce the intervention group to downloading and using the mobile application. After logging into the app, the patients can use the application during the following 12 months. Related conversations with rehabilitants show that the use of a mobile application can expect high acceptance.

Furthermore, ReNaApp contains additional features that are not included in “Neues Credo”. First, the app automatically generates feedback in relation to the executed physical activities. Replacement of the classic paper-based activity diary with ReNaApp, involves changes in both the medium and the time interval of the feedback. Concerning the participants’ activities, the type and frequency of notifications are adapted by the app. In the aftercare period, the rehabilitants receive motivational letters from their aftercare agents at regular intervals (after 3, 6 and 9 months). In particular, the letters refer to maintaining physical activity or encouraging the rehabilitants to be more active.

In addition, the control group obtains the standardized therapy during rehabilitation as well as in aftercare. During rehab, the patients supply care from their clinic regarding the existing standards. The Sixth Social Code implies that only functional training or rehabilitation sports are offered to oncological rehabilitants after rehab.

### Mobile application

All rehabilitants of the intervention group document their physical activity in the exercise diary in ReNaApp. This flexible procedure ensures that the quality and functionality of the mobile application works permanently.

The currently available smartphones have a high degree of heterogeneity in brand, performance, display size, and software, with diverse operating systems. To include the largest possible number of smartphone users, ReNaApp uses frameworks and APIs that ensure compatibility with both iOS and Android operating systems, which include the vast majority of potential users’ devices. Because of impressive graphical frameworks and innovation in web technology, ReNaApp will be designed as a progressive web application (PWA) with a responsive design for automatic screen adaption [29, 30] and complete offline availability. This also ensures a convenient way for installing the app while allowing the project owners to keep complete control of the distribution of the software.

The user-centred design approach DIN EN ISSO 9241–210 [31] ensures high usability and acceptance for mobile applications. In particular, breast cancer patients are involved throughout the whole process. First, the user-centred design approach includes the planning of the design process as well as the empirical specification of usage requirements. The main stage searches for layout solutions for fulfilment of the usage requirements. In particular, the second phase encompasses the development and design of the human-technology interface of ReNaApp. These solutions will be tested and revised in terms of an iterative formative evaluation. Following a subsequent evaluation in the laboratory, the system will be optimized if necessary.

Like in the exercise diaries on paper, the patients will document their intentions regarding physical activity in ReNaApp. The documentation includes a selection of different types of physical activities, as well as custom activities. Furthermore, ReNaApp reminds the patients of their defined intentions regarding physical activity. Following a planned physical activity, the rehabilitants are requested to document whether they stuck to their plan and practiced physical activity for the full amount of time projected. Moreover, the patients record barriers, promoting factors and alternatives in terms of implementation problems.

An alternative option for tracking physical activity is to connect health tracker devices and integrate their data. Previous research shows that approximately 74% of all these devices belong to either Fitbit or Xiaomi [32]. Fitbit enables the access of collected data using interfaces [33–35] only by connecting to the Fitbit cloud service but not locally via Bluetooth [34]. In fact, most manufacturers give no guarantee for the support of collecting private data directly from end user devices without a cloud connection. Except for some reverse engineering approaches, most of the fitness devices cannot be connected with arbitrary apps via Bluetooth.

The second market leader, Xiaomi, only enables unofficial opportunities to transfer data via Bluetooth [36, 37]. Two recent tests by the paper c’t [33, 38] examined alternative fitness trackers without cloud connections, but these are not represented in the mentioned distribution statistics. Consequently, to integrate fitness trackers, it is necessary to obtain the approval of the users for the initial connection between the devices. This option exists in almost every common fitness tracker. Considering privacy concerns, this study does not pursue the mentioned approach.

To avoid this problem, health-middleware services from both operation systems (Android, iOS), i.e., Google Fit [39] and Apple Health Kit [36], can be used. With these, it is possible to integrate any device by the detour of a middleware approach. Because these are cloud services, privacy concerns with respect to data transfer, processing and storing emerge. Because of these concerns, middleware solutions will not be used.

In addition to the data protection and technical difficulties of connecting fitness trackers, another reason for leaving out these devices is the idea of “Neues Credo”. The users should consciously plan and reflect on their physical activity. The automation of these steps by using a fitness tracker does not follow the aftercare concept. Furthermore, a bias would arise in the intervention group between users with fitness trackers and those without.

The patients constantly evaluate their self-imposed targets at intervals similar to those in the paper-based exercise diary. Based on an algorithm in the app, the patients receive feedback from ReNaApp regarding their documented physical activities in comparison with the recommended time frame [40]. The time intervals for feedback are similar to those of the classic feedback letters. Consequently, ReNaApp takes over this task from the aftercare agents in the post-rehab period.

## Methods

### Eligibility criteria

All patients from our five partner clinics with a reliable diagnosis of breast cancer will be included in this study (C50.0–.9 und D05.0–.9). Moreover, the rehabilitants must be between 18 and 60 years old, own a smartphone and have adequate German language skills.

All rehabilitants who do not have a reliable diagnosis of breast cancer or who abandon rehab are excluded from the study. Other criteria for excluding participants are insufficient German language skills, missing declaration of consent and constraints in physical activity.

### Study design

The study is organized as a mixed-methods study [41] with different methodological components (sections A-D). The leader of the study is the Institute for Social Medicine and Epidemiology of the University of Lübeck. The recruitment takes place in five different rehabilitation clinics in Germany (AMEOS Reha Klinikum Ratzeburg, Klinik Graal-Müritz, Strandklinik Ostseebad Boltenhagen, Asklepios Klinik Am Kurpark Bad Schwartau, Sonneneck Nordsee-Fachklinik Wyk auf Föhr). The designated aftercare agents of each clinic are responsible for the screening of eligible patients within the first days of their rehabilitation. If applicable, the agents address the patients personally and give them the information sheets and the declaration of consent.

### A: quantitative measures

To examine the long-term effects of oncological rehabilitation with ReNaApp, the study is structured as a monocentric, quasi-randomized longitudinal study with three measurement points: at the beginning (t_0_) and end of rehabilitation (t_1_) and 12 months after rehabilitation (t_2_). All patients will complete a written questionnaire using standardized, validated instruments.

Following a sequential design, all rehabilitants who arrive in the rehab clinics belong to the control group (standard therapy and standard aftercare) until the desired number of cases is reached. After the recruitment of the control group, the rehab teams of all clinics are instructed in the handling of ReNaApp and the aftercare philosophy. The implementation of the aftercare intervention is accompanied by a fundamental change in the procedures and therapy regimens in clinics; therefore, recruitment of the control and intervention groups at the same time will not be possible. The later rehabilitants who fulfil the eligible criteria will be allocated to the intervention group. Based on preliminary interviews in rehab clinics, we assume that most of the rehabilitants own a smartphone and know how to use a mobile application.

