The extent of *physical activity* will be assessed in connection with the questionnaire of the Federal Health Survey by Menski, 1998 [57]. In addition, the use of health promotion services will be measured by a questionnaire from the Quality Community for Medical Rehabilitation [52, 56].

The moderating variable is comorbidity [58], as well as risk factors and sociodemographic variables [59]. Table 1 shows the set of the core instruments to be used in the study.

**Table 1 Tab1:** Core set of instruments used in the quantitative part of the study

Dimensions	Instruments	t_0_	t_1_	t_2_
Primary Outcome				
Restriction of Participation	IMET [42]	●		●
Disease-specific Quality of Life	EORTC-QLQ-C30 [60]	●	●	●
	EORTC-QLQ-BR23 [45]			
Return to Work	Single Items			●
Secondary Outcomes				
Ability to Work	Work Ability Score, WAS [61]	●		●
Occupational Stress	SIBAR, II and IV [49]	●		●
Subjective Prognosis of Employment	SPE-Scale [62]	●		●
Occupational Changes	Single Items from QGmR [52]			●
Fatigue	EORTC-FA 12 [54]	●	●	●
Depressive State	CES-D [55]	●	●	●
Performance in Various Areas of Life	QGmR [52]	●		●
Physical Activity	Federal Health Survey [57]	●		●
Use of Health Promotion Services	QGmR [52]	●	●	●
Moderating Variables				
Comorbidity	Single Items [58]	●		●
Living Habits	Single Items	●	●	●
Sociodemographic Data	Single Items [59]	●		●

t_0_ = baseline/right before rehabilitation; t_1_ = 3-week follow-up/right after rehabilitation; t_2_ = 12 months after t_1_

Outcomes that cannot change during rehabilitation will be measured in the beginning and regard only catamnesis. These include outcomes regarding everyday life and the domestic environment of the patients (social participation, efficiency and physical activity in daily life) or insignificantly changed outcomes, such as medically determined comorbidities.

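### The clinics' switch is tied to the end of control recruitment, not to the last control's discharge, so late controls can be exposed, and no item on their ReNaApp use is listed

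*Protocol article*

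**What the plan says.** The section on quantitative measures (A) assigns every arriving patient to the control group "until the desired number of cases is reached". It then states: "After the recruitment of the control group, the rehab teams of all clinics are instructed in the handling of ReNaApp and the aftercare philosophy". Eligible patients who come later form the intervention group. The reason given for this sequence is that "The implementation of the aftercare intervention is accompanied by a fundamental change in the procedures and therapy regimens in clinics", so that "recruitment of the control and intervention groups at the same time will not be possible".

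Under Study design, the aftercare agents are "responsible for the screening of eligible patients within the first days of their rehabilitation". The footnote to Table 1 describes t1 as "3-week follow-up/right after rehabilitation", which puts the stay at about 3 weeks. The last assessment, t2, is set at "12 months after rehabilitation".

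On access, the Intervention section says that "ReNaApp is available on the web page of the involved clinics". It adds that patients use the app after logging in, and that the agents introduce it to the intervention group in the class hour. The section on the mobile application says that the chosen technology leaves control of distribution with the project owners. Neither place says who can obtain a log-in.

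**The concern.** The protocol's reason for not recruiting both groups together is that the programme changes how the whole clinic works. The same reason applies to treating both groups together. Yet the trigger is the end of control recruitment, and a woman recruited in her first days still has most of her stay ahead of her. Nothing in the article ties the switch to the discharge of these women.

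A second route opens after discharge. Controls are followed for a year under standard aftercare, and during that year the app is offered on the web pages of the clinics where they were treated. All of them own a smartphone, because that is an eligibility criterion.

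Controls who take up parts of the programme would still be counted as standard care. If the programme works, this narrows the contrast on the primary outcomes, and the same effects feed the cost-effectiveness analysis. The adjustment described under Limitations (covariates or propensity score matching) deals with differences in patient and disease characteristics between the groups, not with contamination of the control arm. Table 1 lists no item on ReNaApp use. The Limitations section also says that personal data never pass from the app to the study leader or the agents, so app records are unlikely to identify control users.

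**Working it through.** **Inputs from the protocol article**
- Stay from t0 to t1: about 3 weeks (Table 1 footnote).
- Follow-up: 12 months, taken as 52 weeks, after t1.
- Effect size 0.40, two-sided alpha 1.6%, power 80%, net 235 per group, 30% dropout, 10% matching allowance, 370 per group (sample size section).

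**Assumptions**
- Control recruitment lasts T weeks at an even rate. The article gives no duration, so T runs from 26 to 104.
- For the upper bound, the switch is immediate and every control in house receives the full effect.

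**The plan's own figures.** The inflation steps reproduce: 235/0.7 = 336 (rounded), and 336 × 1.1 = 369.6, so 370. The net size does not. With n = 2(z₁₋α/₂ + z₁₋β)²/ES², an effect size of 0.40 gives 133 per group, while 0.30 gives 235. That is a separate matter, but it is why power is shown below under both values.

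**Formulas**
- Share in house when recruitment ends = 3/T; number = 370 × 3/T.
- Lowest effect size = 0.40 × (1 − 3/T).
- Power at 235 per group = Φ(ES × √(235/2) − z₀.₉₉₂), with ES = 0.40 or 0.30, each multiplied by (1 − 3/T).
- Share of controls with follow-up still open at the trigger = min(1, 55/T), where 55 = 3 + 52 weeks.

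| T (weeks) | In house | Of 370 | Lowest ES (from 0.40) | Power, true ES 0.40 | Power, true ES 0.30 | Follow-up still open |
|---|---|---|---|---|---|---|
| 26 | 11.5% | 43 | 0.354 | 92% | 68% | 100% |
| 39 | 7.7% | 28 | 0.369 | 94% | 72% | 100% |
| 52 | 5.8% | 21 | 0.377 | 95% | 74% | 100% |
| 78 | 3.8% | 14 | 0.385 | 96% | 76% | 71% |
| 104 | 2.9% | 11 | 0.388 | 96% | 77% | 53% |

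Without dilution, power at 235 per group is 97% for 0.40 and 80% for 0.30.

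The bound is generous. Under even recruitment, women in house at the trigger have on average half their stay left. If exposure scaled with the remaining stay, the effect size would be 0.40 × (1 − 1.5/26) = 0.377 at 26 weeks and 0.40 × (1 − 1.5/104) = 0.394 at 104 weeks.

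The last column shows only how many controls could come across the app during follow-up. It says nothing about how many would use it, and the documents give no uptake figure.

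**The case against.** A reader might infer that the late controls are in fact exposed and that controls in follow-up have free use of the app. The documents do not support either. The text places staff instruction after control recruitment, not immediately after it. No start date for the new regimen is given, and teams in five clinics must first be instructed. A gap is not described, but it is not excluded. The planning group and the app introduction come at the end of an intervention patient's stay; since those patients arrive after the last controls, most late controls would be leaving or gone by then. Agent support and the app introduction are expressly tied to the intervention group, and controls are assigned standard therapy and standard aftercare. A log-in is required, and the owners keep control of distribution. Rules for issuing log-ins are a detail that an article may leave to the full protocol.

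Nor are the t2 data wholly blind. Use of health promotion services and physical activity are measured, and patients report their use of services. Table 1 is also headed as a core set, so the full questionnaire may hold more.

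All of this stands as a limit on the size of the problem. It does not remove the point. The rule as written allows an overlap that the protocol's own reasoning counts as a problem. Informal spill-over from newly trained staff does not depend on the group hour. The listed t2 measures are not specific to ReNaApp.

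**Conclusion.** The point holds as a weakness in a stated rule, not as evidence of contamination. The trigger allows the last controls to be treated in a clinic that has already begun to change. The app can be met on clinic web pages during the follow-up of many or all controls, and no listed measure would show whether controls used it.

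The in-house part is small: about 12% to 3% of controls for recruitment over 26 to 104 weeks, with an effect size of 0.40 falling to about 0.35 at worst. This rests on assumed even recruitment, an immediate switch and full effect in every control in house. At the planned 235 per group, power stays at 92% or more if the true effect is 0.40. It drops from 80% to between 68% and 77% only if the true effect is 0.30. The web-page part could reach more women, from 53% to all of the controls, but its effect cannot be sized because uptake is unknown.

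If the programme works, any bias is toward no difference. The correction is cheap enough that it should be made.

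**What to change.** - In the section on quantitative measures, change the trigger: staff instruction and intervention recruitment start in a clinic only after its last control has completed t1 and been discharged. This costs a recruitment pause of about 3 weeks per clinic.
- Add one item to the control group's t2 questionnaire: use of ReNaApp or the observation book, yes or no. Report the share exposed, with a sensitivity analysis that leaves out exposed controls. Treat that analysis as supportive, since women who seek out the app may differ from those who do not.
- Confirm that log-ins are issued only to intervention participants until control follow-up ends. If the full protocol already says so, a sentence in the article is enough.

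No extra patients or staff are needed. If the switch has already taken place, report for each clinic the date of staff instruction and the date of the last control's discharge, so that the overlap can be counted.
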